### Sample size and Recruitment

#### Sample size calculation

The power analysis for sample size is based on the difference between the adherence score after implementation of CHEP and the adherence score at baseline using the 5-item Morisky adherence scale. Using the Morisky distribution of low, medium, and high adherence ratios of 32%, 52% and 16% respectively [14], and an estimated post CHEP effect shift of 10% to a higher category, we will need a minimum sample size of 150 patients.

#### Patient recruitment

The following steps will be applied in recruiting patients for the CHEP study:

1. Researchers will use the records of the QUICK - I study to identify all patients with uncontrolled hypertension or with low or medium adherence scores for medication or other life style measures on the Morisky Scale at 12 months after inclusion into the study.

2. Eligible patients will be informed about QUICK-II and invited for participation through a written invitation.

3. A research assistant will assess patients who are interested in participating for eligibility criteria and eligible patients will be asked to give informed consent.

4. Patients who give informed consent will be invited to a one-hour baseline assessment session.

5. Included patients who have completed baseline assessments will be invited to have three CHEP sessions spaced over a period of 4 months and one final assessment interview six months after baseline.

To encourage participation, all included patients will be reimbursed for extra travel costs incurred in visiting for assessments and CHEP sessions outside their normal clinic days.

### Intervention

The intervention (CHEP) will be developed in part 1 of this project. Subsequently, patients will be given (i) three CHEP sessions over a period of four months conducted by a trained nurse; (ii) audio-visual or written educational materials containing specific information for the target group and (iii) if necessary, referrals to regional facilities or initiatives that may help patients to adopt healthier lifestyles.

#### Sessions

The first session will take place two weeks after the baseline assessment interview, and the next two sessions will occur one and three months thereafter. Clinical guidelines generally recommend a patient centred approach as the preferred strategy for supporting patients in achieving CVD treatment goals, such as adherence to prescribed medication, dietary changes, and weight reduction, reduced sodium intake, increased physical activity and moderate use of alcohol [3]. While CHEP will use this framework, it will have the additional aim of eliciting and discussing culturally and socially specific aspects of patients' perceptions of cardiovascular risk factors and treatment. This method is based on the work of Arthur Kleinman [15], as well as more recent approaches to improving adherence in hypertensive patients of various ethnic and geographical background, such as those recently developed in The Netherlands [16]. In short, after identifying potential communication barriers and establishing a rapport with the patient, it is expected that the first session will focus on the patient's beliefs about hypertension. The next two sessions will deal with the daily challenges they face in achieving hypertension treatment goals within the broader context of their lives. Education will take place in group training sessions.

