## Methods

### Project design

#### QUICK - II consist of two consecutive parts

In *part 1 *of the study, we will develop a stakeholder based Cardiovascular Health Education Program (CHEP) that is to be used to educate patients at risk of CVD who are enrolled in a private health insurance plan in rural Nigeria. To develop CHEP, we will use the following step-wise approach: (i) open qualitative interviews will be conducted with key stakeholders in CVD care to explore their perceptions on CVD, CVD risk factor management and CVD prevention and care. These stakeholders include patients at risks for CVD, healthcare providers (HCP), and health insurance managers of HCHP; (ii) on the basis of the outcomes of interviews with patients, CHEP will be developed; (iii) supportive strategies needed to implement CHEP successfully will be identified on the basis of the outcomes of the interviews with HCP and health insurance managers.

In *Part 2 *of the study we aim to evaluate the effect of CHEP through a prospective hospital-based study, using a pre-post intervention design. Measurements will be conducted in a subset of patients included in QUICK - I: those who have uncontrolled hypertension or other CVD risk factors, or are non adherent to medication after 12 months of treatment.

In addition, case file data will be reviewed and interviews with health care professionals in the participating clinic will be held and analyzed to evaluate the feasibility of the application of CHEP in practice.

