### Data Analysis

#### Statistical methods

The rate of adherence will be examined according to the intention to treat principle. Primary and secondary outcome measures will be calculated for every patient at baseline and 6 months thereafter to assess possible improvements. Furthermore, univariate and multi-level analyses will be performed to evaluate the modifying effect of the outcome measures (see above) on adherence or blood pressure. If the N is sufficient, we will perform separate subgroup analyses for gender. While a *p *value of 0.05 will be the critical value for all analysis, the *p *value will be adjusted for subgroup analysis according to standard procedures.

Data from interviews with HCP will be analyzed and used to identify potential barriers to the implementation of CHEP in practice.

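### CHEP is taught in groups, but the sample size of 150 makes no allowance for within-group correlation, and the planned multilevel analysis is not tied to education group or to the primary 6-month change

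*Protocol article*

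**What the plan says.** Part 2 is a single-arm evaluation in one hospital, "using a pre-post intervention design". Under Intervention, patients receive "three CHEP sessions over a period of four months conducted by a trained nurse", and the Sessions subsection adds: "Education will take place in group training sessions". The article does not give the size or number of groups, the number of nurses, or whether a patient stays in the same group for all three sessions.

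The Sample size calculation is based on the "difference between the adherence score after implementation of CHEP and the adherence score at baseline using the 5-item Morisky adherence scale". Its inputs are "low, medium, and high adherence ratios of 32%, 52% and 16% respectively" and "an estimated post CHEP effect shift of 10% to a higher category", and it concludes: "we will need a minimum sample size of 150 patients". No clustering term appears.

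On analysis, Statistical methods says: "Primary and secondary outcome measures will be calculated for every patient at baseline and 6 months thereafter to assess possible improvements". It then adds univariate and multi-level analyses, with the purpose of studying modifying effects on adherence or blood pressure. The Analysis line of the abstract gives the same two kinds of analysis a wider purpose, namely the outcomes of the intervention. Neither place says what the levels are.

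**The concern.** The sessions are meant to draw out and discuss patients' beliefs and daily difficulties, so exchange between patients is part of how the programme works. Patients taught together share that discussion and the educator, and their changes in adherence may therefore be more alike than those of patients taught apart. The Discussion accepts that patients talk to each other about their condition and treatment and uses this as a reason not to randomise, but the sample size does not take it up.

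With no control group, the claim of effect rests largely on the mean pre-post change and its standard error, judged at p = 0.05. If that standard error is computed as though 150 patients contributed independent changes when they did not, it is too small. The multilevel plan could deal with this, but it does not as written. In a one-hospital study with two time points, the levels could simply be visits within patients, which would leave education group out.

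**Working it through.** **1. Can 150 be reproduced, and does it contain a clustering allowance?** Power, sidedness, the test and the pre-post correlation are not stated, and a 10% shift can be read in several ways. Take one reading, ten percentage points at each step, so that 32/52/16 becomes 22/52/26, with two-sided alpha 0.05 and an assumed power of 80% (z values 1.96 and 0.8416):

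- One-sample proportion, low category: [(1.96·√(0.32·0.68) + 0.8416·√(0.22·0.78)) / 0.10]² = 159.5, so 160.
- One-sample proportion, high category: [(1.96·√(0.16·0.84) + 0.8416·√(0.26·0.74)) / 0.10]² = 118.3, so 119.
- Paired mean of a 0/1/2 category score: the mean rises from 0.84 to 1.04 and the variances are 0.4544 and 0.4784. With n = (1.96 + 0.8416)² · Var(change) / 0.20², the result is 184, 129 or 92 for a pre-post correlation of 0, 0.3 or 0.5.
- Chi-square goodness of fit, 2 df: 103.

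Other readings of the shift and 90% power were also tried. No fully specified variant came within 3% of 150 (145.5 to 154.5). McNemar's test with a net shift of 0.10 gives 147 if 19% of patients are discordant, but the article gives no discordance. So 150 cannot be derived uniquely. None of these calculations contains a clustering term, and the paragraph lists no input from which one could be built.

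**2. What would clustering do to 150?** Let m be patients per group and ICC the intraclass correlation of the change. Groups form after baseline, so it is the change, or the 6-month score, that matters. Both m and ICC are assumptions.

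Design effect DE = 1 + (m − 1)·ICC; effective n = 150/DE; correct interval width relative to the naive one = √DE; actual level of a nominal 5% test that ignores groups = 2·[1 − Φ(1.96/√DE)].

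| m | ICC | DE | Effective n | Width factor | Actual level |
|---|---|---|---|---|---|
| 5 | 0.01 | 1.04 | 144 | 1.02 | 5.5% |
| 10 | 0.02 | 1.18 | 127 | 1.09 | 7.1% |
| 10 | 0.05 | 1.45 | 103 | 1.20 | 10.4% |
| 10 | 0.10 | 1.90 | 79 | 1.38 | 15.5% |
| 15 | 0.05 | 1.70 | 88 | 1.30 | 13.3% |
| 20 | 0.05 | 1.95 | 77 | 1.40 | 16.0% |
| 20 | 0.10 | 2.90 | 52 | 1.70 | 25.0% |

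At ICC = 0 nothing changes. If 150 had been chosen for 80% power, which the article does not say, power would be about 78% in the first row, 73% and 64% with 10 per group at ICC 0.02 and 0.05, and 38% in the last row.

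**3. Number of groups.** 150/5 = 30, 150/10 = 15 and 150/20 = 7.5. With 15 groups or fewer, the analysis also needs a small-sample correction.

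**4. The two statements on multilevel analysis, side by side.** The abstract's purpose would cover the primary change. In Statistical methods, the multi-level analyses are introduced as a further step after the outcomes have been calculated, and are directed at effect modification. A reader following Statistical methods would have no instruction to account for education group in the primary comparison. Table 3 lists no group or nurse identifier, although its process-data row is open-ended, so this only supports the point.

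**The case against.** A reader might infer that the plan treats the 150 patients as independent, and so that its confidence intervals will be too narrow. The documents do not support that. The abstract plans multilevel analysis for the intervention's outcomes, and an unnamed level could be education group. Calculating outcomes for every patient is also compatible with a model that has a group effect. No primary test or variance estimator is stated. Too-narrow intervals require both a positive ICC and an analysis that ignores groups, and the article establishes neither.

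A reader might also infer that 150 is too few. That cannot be shown. No power is stated, and several readings in the working need fewer than 150 without clustering: 129 and 92 leave room for design effects of 150/129 = 1.16 and 150/92 = 1.63. Other readings need more than 150.

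The actual test levels in the table need a qualification. If CHEP changed nobody's adherence, shared teaching by itself would create no within-group correlation. The figures apply to a null in which the average effect is zero but the effect varies between groups, or in which groups share something else that moves their scores.

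Finally, random-effect structure and degrees of freedom are usually left to an analysis plan, and the missing control group, which the article acknowledges, is the larger limitation. Both are fair. What stands is narrower: the stated minimum was fixed with no sign that group delivery was considered, and the article's two statements on multilevel analysis differ in purpose and leave the primary change uncovered in the section that governs analysis.

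**Conclusion.** The point holds in a conditional form. Group delivery is stated, the sample size paragraph makes no allowance for it, and nothing ties the planned multilevel analysis to education group or to the primary 6-month change. Following Statistical methods as written can therefore understate the standard error, and any positive ICC of the change puts the effective size below 150.

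The size of the loss rests wholly on an assumed group size and ICC. Over 5 to 20 per group and ICC 0.01 to 0.10 it runs from negligible (effective n about 144, interval 2% wider) to severe (about 52, 70% wider). With 10 per group and ICC 0.02 to 0.05, effective n is about 127 to 103 and the interval 9% to 20% wider. It is worth correcting before sessions start, because group membership is hard to reconstruct if it is not recorded then.

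**What to change.** - Record education group and nurse for every patient at every session.
- Estimate the primary and secondary baseline-to-6-month changes with education group as a random effect and small-sample degrees of freedom, or with cluster-robust standard errors suitably corrected for the number of groups. If patients move between groups, specify in advance either a multiple-membership model or grouping by first session.
- Make the abstract and Statistical methods agree on what multilevel analysis is for, and name education group as a level.
- State the planned group size and restate the precision that 150 gives at that size over a stated ICC range. This does not call for enrolling more patients.

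The cost is a group and nurse entry in the session record, one model term, and a somewhat wider confidence interval if the correlation is positive.

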#### Educational materials

Patients will also be given information leaflets or audio visual materials that provide answers to frequently asked questions about hypertension. These will be designed to address the specific languages, customs, habits, norms and dietary cultures that characterize the communities of the patients participating in the program.

#### Supporting healthier lifestyles

If necessary, patients will be referred to initiatives offering healthier lifestyle support that is tailored to the target group, based on a referral list that will be established for this purpose in the first part of this study.

#### The nurses

In order to ensure treatment fidelity and to avoid organizational- and healthcare-related obstacles to implementation, the nurses who will provide CHEP will be given clear guidelines and extensive training in implementing these guidelines.

### Materials and Measurements

We will use the following measurements and materials to evaluate the effects of CHEP: patients' adherence to medication and other life style recommendations will be measured by using the five point Morisky Scale; and patients' blood pressure will be measured using pre validated OMRON M6 Comfort electronic equipment. The blood pressure will be measured on 3 occasions with the patient seated comfortably for 5 minutes, and the last two values averaged. All other physiological measures will be performed according standardized procedures using standard equipment. Other self-reporting measures (see Table 3) will be measured using the questionnaire of the OHD 2 trial in the Netherlands [16]. Aspects of this questionnaire will be adapted to the Nigerian specifics where necessary.

**Table 3 T3:** Timelines and measures used in CHEP study

Measures	Baseline	Final
Physiological measures		
- Clinic BP measurements, Heart rate	X	X
- Height, weight, Body Mass Index	X	X
- Hip and waist circumference	X	X

Self-reporting measures		
- Patient demographics	X	
- Additional cardiovascular risk factors (physical activity, diet, smoking, alcohol, sodium intake)	X	X
- Medication adherence	X	X
- Adherence to lifestyle recommendations	X X	X X
- Knowledge of HTN	X	X
- Perceptions of HTN	X	X
- Perceptions of medication	X	X
- Self efficacy	X	X
- Satisfaction with care	X	X
- Perception of stress	X	X

Case file data		
- Prescribed medication	X	X
- Prescribed lifestyle measures	X	X
- Co-morbidity	X	X

Process data		
- Records office visits, patient drop-out data etc	X	X
- HCP interviews		X

All assessments will take place at baseline and 6 months after. A trained nurse will perform all physiological assessments. A trained interviewer will perform pre- and post CHEP assessment interviews. The researcher will be responsible for the training of the nurses and the interviewers.

Table 3 presents all the measurements that will be used in the study.

### Data Analysis

#### Statistical methods

The rate of adherence will be examined according to the intention to treat principle. Primary and secondary outcome measures will be calculated for every patient at baseline and 6 months thereafter to assess possible improvements. Furthermore, univariate and multi-level analyses will be performed to evaluate the modifying effect of the outcome measures (see above) on adherence or blood pressure. If the N is sufficient, we will perform separate subgroup analyses for gender. While a *p *value of 0.05 will be the critical value for all analysis, the *p *value will be adjusted for subgroup analysis according to standard procedures.

Data from interviews with HCP will be analyzed and used to identify potential barriers to the implementation of CHEP in practice.

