### Outcomes

The primary outcome of the evaluation of CHEP will be the changes in adherence to medication or life style recommendations. This will be assessed through the Morisky self-report medication adherence questionnaire [14]. This scale asks patients to respond yes or no to five questions. Each positive answer is assigned a score of one, with higher scores indicating poorer adherence. The same scale will be used for other life style recommendations (e.g. salt intake). As such, self-reported adherence will be assessed as a continuous measure.

Secondary outcomes are changes in physiological measures - systolic blood pressure, diastolic blood pressure, and body mass index (BMI) or abdominal obesity at 6 months after baseline.

Table 2 indicates definitions of what we consider as significant improvement per outcome measure.

**Table 2 T2:** Definitions of significant improvement per outcome measure

Outcomes	Significant improvement
Adherence to medication and life style recommendations (Primary outcomes)	Using the distribution on the Morisky scale [14] of low, medium, and high adherence ratios, a post CHEP effect shift of 10% to a higher category will be defined as a significant improvement in adherence.

Blood pressure (Secondary outcome)	Blood pressure decrease of >10% systolic or diastolic or blood pressure at target level (patients without diabetes or established CVD: <140 mmHg systolic and <90 mmHg diastolic, patients with diabetes, renal disease or established CVD: <130 mm Hg systolic and <80 mmHg diastolic).

Body mass index (kg/m^2 ^)	No CVD risk: <25 Moderate CVD risk: 25-30 High CVD risk: >30 In patients with a BMI >25 any reduction of BMI at 6 months will be regarded as an improvement.

Data will also be collected about other factors that may influence patients' hypertension management: self-reported cardiovascular risk factors (physical activity, diet, smoking, alcohol, sodium intake), knowledge of HTN and HTN management, perceptions of HTN, perceptions of medications, self efficacy, experienced stress, patient satisfaction with care (e.g. doctors' performance, supply of medication, frequency of follow up, satisfaction with CHEP etc).

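### The gender analyses are planned separately for men and women with no direct comparison between them, so any statement about a gender difference should rest on a gender-by-time estimate

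*Protocol article*

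**What the plan says.** The article's section on the two parts of QUICK-II describes the evaluation as a prospective hospital-based study "using a pre-post intervention design". There is no control group, and the Discussion acknowledges this as a limitation. On the endpoint, the Outcomes section states: "The primary outcome of the evaluation of CHEP will be the changes in adherence to medication or life style recommendations".

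The Statistical methods section covers gender in one sentence: "If the N is sufficient, we will perform separate subgroup analyses for gender". On significance, it says that a p "value of 0.05 will be the critical value for all analysis", and that for subgroups the p "value will be adjusted for subgroup analysis according to standard procedures". It names neither the subgroup test nor the adjustment.

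No direct comparison of men with women appears anywhere in the article. The univariate and multi-level analyses in the same section examine whether the outcome measures modify adherence or blood pressure. Gender is not named there.

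**The concern.** In a one-group study with two time points, an analysis run separately in each gender is most naturally a test of change from baseline within men and another within women. The p-value adjustment indicates that these results will be tested for significance and not only described.

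Each test asks whether that gender changed. Neither asks whether the two genders changed by different amounts. With about half the patients in each analysis, one test can easily reach significance and the other miss it when the true change is identical. Adjusting the p values limits false positives within each gender but leaves the between-gender question untested. At stake is how a result that is significant in one gender only would be interpreted.

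**Working it through.** **The plan's own figure.** The only sample size is for the overall comparison: "we will need a minimum sample size of 150 patients". Its inputs are "Using the Morisky distribution of low, medium, and high adherence ratios of 32%, 52% and 16% respectively" and "an estimated post CHEP effect shift of 10% to a higher category". Power, sidedness, the test and the pre-post correlation are not given. Several standard formulas were tried and none returned 150. Among those that come close:

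- paired mean category score, 32/52/16 moving to 22/52/26, correlation 0, one-sided, 80% power: 145;
- McNemar with 15% improving and 5% worsening, two-sided, 80% power: 155;
- one-sample proportion, 32% to 22%, two-sided, 80% power: 160.

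So 150 can be neither confirmed nor refuted, and overall power has to be assumed below. No figure is stated for the gender analysis.

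**Inputs.** From the article: 150 patients and a critical value of 0.05. Assumed: two-sided tests, overall power, a gender split between 50:50 and 30:70, Bonferroni adjustment (0.025 per gender) as the alternative to 0.05, the same true change and variability in both genders, and a normal approximation.

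**Power within one gender.**

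- Non-centrality of the overall test at 80% power: 1.96 + 0.84 = 2.80.
- In a share f of the sample it becomes 2.80 × √f. For half (75 patients): 2.80/√2 = 1.98.
- Power at 0.05: Φ(1.98 − 1.96) ≈ 0.51.
- Power at 0.025: Φ(1.98 − 2.24) ≈ 0.40.

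**Chance that exactly one gender is significant.** Men and women are different patients, so the tests are independent and the chance is p_m(1 − p_w) + p_w(1 − p_m).

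- Even split at 0.05: 2 × 0.508 × 0.492 = 0.50.
- Even split at 0.025: 2 × 0.397 × 0.603 = 0.48.
- No true change, at 0.05: 2 × 0.05 × 0.95 = 0.095. At 0.025: 2 × 0.025 × 0.975 = 0.049.

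| Assumed overall power | Split | 0.05 each | 0.025 each |
|---|---|---|---|
| No true change | any | 9.5% | 4.9% |
| 50% | 50:50 | 40.6% | 31.5% |
| 80% | 50:50 | 50.0% | 47.9% |
| 80% | 30:70 | 54.9% | 52.1% |
| 90% | 50:50 | 46.6% | 49.9% |
| 90% | 30:70 | 54.0% | 56.5% |
| 99% | 50:50 | 24.4% | 33.7% |
| 99% | 30:70 | 36.5% | 46.5% |

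Adjustment barely moves the figure at 80% overall power and raises it at 90% and 99%.

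**The direct test.** At 0.05, a test of the gender difference in change has a 5% false-positive rate by construction. Its power is limited. With an even split, each gender's standard error is √2 times the overall one, so the standard error of the difference is √2 × √2 = 2 times the overall one. For a gender difference as large as the whole design effect at 80% overall power, non-centrality is 2.80/2 = 1.40 and power is Φ(1.40 − 1.96) ≈ 0.29.

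**The case against.** The article does not name the subgroup test. Reading it as within-gender pre-post tests is an inference, and a fuller analysis plan could add a gender-by-time term. The inference is nonetheless the plain one for separate analyses in a one-group pre-post study, and the criticism is of a stated method, not of missing detail.

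A reader might infer that, followed as written, the plan will conclude that the programme works in one gender only. The article does not support that. It sets no rule for comparing the two p values, states no aim of showing a gender difference, and does not say why the gender analyses are run. Describing change in each gender is a legitimate purpose. The misreading is left open, not planned. Nor does the article support a link to gender-specific roll-out: the Discussion expresses only a general hope of wider use.

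It would also be too strong to say that separate analyses can never inform the question. Two independent estimates with standard errors can be compared; the plan just does not say that they will be.

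A reader might suspect that the condition on N lets the analysis be run or dropped once results are seen. The condition concerns numbers, not results. Demographics are recorded at baseline (Table 3), so numbers by gender can be known before any six-month outcome. The missing threshold is a minor matter of detail.

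Finally, the figure of about one half depends on assumed power and on there being a real change.

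**Conclusion.** The point holds in a limited form. The article plans separate, multiplicity-adjusted analyses by gender and names no comparison between them. Such tests do not show whether change differs by gender, and the p-value adjustment does not supply that comparison.

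With an identical true change and 80% to 90% overall power, exactly one gender would be significant in about half of studies (47% to 57% across the splits and critical values examined). That range should not be quoted without its assumptions, because the article states neither power nor gender split, and the figure is far lower when nothing changes. The problem matters only if a result significant in one gender alone is presented as a gender difference.

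Because Part 2 has no control group, no gender analysis here can establish that the programme itself works differently in men and women. This is a conditional, secondary analysis and does not affect the primary comparison. It is still worth correcting, because the correction costs almost nothing.

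**What to change.** State that any statement about a gender difference will rest on one gender-by-time interaction, or equivalently a comparison of change scores between men and women, reported with its 95% confidence interval and labelled exploratory. Report the change within each gender with a confidence interval as descriptive only. Add that, without a control group, the interaction shows a difference in change over time and not a difference in programme effect.

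The cost is a sentence or two and one simple model or comparison, using gender and the baseline and six-month scores already to be collected. The drawback is imprecision: the low power calculated above means that a wide interval including zero must not be reported as evidence that men and women respond alike.
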